### Data sources

2.3

To obtain a large and geographically diverse population, data will be extracted from data sources in the US and several European countries (Germany, Italy, Sweden, and the UK). Table 3 presents detailed information on each database, along with projected numbers of patients initiating ticagrelor 60 mg ≥1 year after their most recent MI available at the time of data extraction. In general, the study will use data on inpatient and outpatient care, prescriptions, and mortality when available. An estimated total of 7250 patients prescribed ticagrelor 60 mg are expected to be included across databases.

**TABLE 3 clc23702-tbl-0003:** Description of databases in each country

Country	Database(s)	Number of unique patients and National coverage (approximate)	Projected number of patients at time of data extraction^a^
US	Optum Clinformatics® administrative claims database combines data from over 50 healthcare providers in the US (>700 hospitals and 7000 clinics). The database provides a single‐payer view of data on demographics, diagnoses, and procedures performed during outpatient visits (outpatient specialist and physician visits) or inpatient stays, and outpatient prescription records (i.e., date of dispensed prescriptions). As is typical for US commercial claims databases, comprehensive data on mortality is not available in the Optum Clinformatics database.	180 million; 55%	750
	IBM's MarketScan Commercial Claims and Medicare Supplemental database consists of administrative claims submitted from US inpatient and outpatient encounters, as well as pharmacy claims (i.e., date of dispensed prescriptions). Medical claims are linked to outpatient prescription drug claims and person‐level enrollment information. The MarketScan supplemental database profiles the healthcare experience of retirees with Medicare supplemental insurance paid by employers. The Medicare Supplemental database provides data on medical and pharmacy claims for healthcare services performed in both inpatient and outpatient settings (i.e., date of dispensed prescriptions). As is typical for US commercial claims databases, comprehensive data on mortality is not available in the MarketScan database.	203 million; 62%	1200

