	Medicare health insurance database covers fee‐for‐service claims data of individuals who are aged ≥65 years, select individuals with disabilities aged <65 years, and those with end‐stage renal disease. The data cover beneficiaries' encounters with the healthcare system and receipt of therapeutic interventions, including medications (i.e., date of dispensed prescriptions), procedures, and services. Data on mortality are available.	62 million; 19%	3100
UK	CPRD GOLD contains longitudinal primary care data from over 800 general practices, whereas CRPD Aurum holds anonymized, longitudinal, primary care patient records collected from over 1100 general practices. Data includes information on patient characteristics and issued prescription medicines. HES covers data on diagnoses and procedures for all hospitalization episodes from England, whereas ONS covers information on all‐cause and cause‐specific death. Data from both HES and ONS will be linked to primary care data of the CPRD. After removal of duplicates, GOLD and Aurum primary care databases will be used for the analysis.	13.5 million; 24% (GOLD+Aurum)	250
Sweden	The National Patient Register includes information on hospital discharge diagnoses and procedures. The Swedish Prescribed Drug Register covers data on all prescribed medications purchased at Swedish community pharmacies. The Cause of Death Register includes information on date and cause of death. The registers are linked by the register holder via the unique personal identification number.	10 million; >99%	800
Germany	AOK PLUS covers longitudinal claims data submitted from primary, secondary, and tertiary care, and contains information on patient demographics, inpatient hospitalizations, outpatient visits, procedures, mortality (inpatient and outpatient date of death), and outpatient prescriptions dispensed in pharmacies.	3.5 million; 4%	150
Italy	ReS database includes data on patient demographics, pharmacy‐dispensed prescription drugs, inpatient diagnoses and procedures, and date of in‐hospital mortality. For deaths in the outpatient setting, neither date of death nor cause of death is recorded in ReS.	5.5 million; 10%	1000
**Total estimated number of patients included across databases** ^a^			**7250**

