### Clinical outcomes

2.5

Study measures, including outcomes, are defined using diagnosis, procedure, and medication codes in the formats used in each database; full definitions are presented in Table S1.

To ensure sufficient precision, clinical outcomes for all study populations will only be analyzed if the a priori threshold of 5000 person‐years on‐treatment with ticagrelor 60 mg is met in the Primary population, as a total across all data sources.

The primary outcome, bleeding requiring hospitalization, is defined as an inpatient admission with at least one overnight stay with a primary diagnosis of bleeding. In a sensitivity analysis, the primary bleeding outcome is defined as bleeding events associated with an inpatient admission of ≥2 overnight stays. Additional bleeding outcomes include the individual components of the primary outcome (hospitalization for intracranial hemorrhage, gastrointestinal bleeding and other bleeding, respectively), bleeding episodes not requiring hospitalization, and fatal bleeding.

Outcomes were identified on the event date recorded in the EHD; for composite outcomes, the earliest date of any of the components was used to define the event date. The secondary CV composite outcome is defined as the composite of hospitalization for MI or stroke, and all‐cause mortality. Additional outcomes include the individual components of the secondary CV composite outcome, three‐point MACE (composite of hospitalization for MI or stroke, and CV death), hospitalization for ischemic stroke, CV death, as well as coronary heart disease (CHD) death. To ensure harmonized definitions across all databases, fatal bleeding, CHD death, and CV disease (CVD) death are defined as death within 28 days of an inpatient hospital admission with a primary diagnosis of bleeding, CHD, and CVD, respectively. Sensitivity analyses for these outcomes will be performed in databases reporting cause of death from death certificates (UK and Sweden). Exploratory outcomes include dyspnea and lower‐limb amputation, as well as bleeding requiring transfusion (only available in the US databases).

Due to insufficiently detailed clinical data in all databases to adequately adjust for imbalances in clinical characteristics between cohorts for comparative analyses, clinical outcomes will only be analyzed in the ticagrelor 60 mg cohorts (i.e., not in the reference cohorts).

Subgroup analyses of interest are described in Figure 2.

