The primary outcomes analyses will be based on an on‐treatment approach, censoring at treatment discontinuation. Additionally, an intention‐to‐treat approach will be used as a sensitivity analysis for the primary bleeding outcome and the secondary CV composite outcome. Sensitivity analyses will also be performed using two alternative definitions of treatment discontinuation, where the grace period is defined as 60 days in all databases, or where the discontinuation date is defined as the date of the last prescription of ticagrelor 60 mg plus half the number of days' supply in that last prescription plus 7 days.

Meta‐analyses will be applied to combine estimates derived from each country/database. Each meta‐analysis will be preceded by an assessment of heterogeneity in terms of patient characteristics and estimates. Heterogeneity will be quantified by the *I*
^2^‐statistic,^19^ and reasons for any observed heterogeneity will be explored prior to estimating the components of the meta‐analysis. A fixed‐effects approach will be used as the main method; random‐effects analyses will also be performed. The meta‐analysis results will be presented in Forest plots displaying the individual database‐level estimates with corresponding 95% CIs.

Regression models combined in the meta‐analyses will use predefined sets of covariates. These covariates will be selected based on the results of the country‐level regression models and clinical knowledge.

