^2^‐statistic for meta‐analyses intends to mitigate and quantify heterogeneity across databases. While outcomes based on cause of death will be defined using the same definition across all databases to ensure harmonization, the contextualization of these findings with sensitivity analyses using data from death certificates (available from UK and Sweden) will be a valuable contribution in advancing methodology in observational studies. Third, the European databases included in this study do not contain comprehensive information on blood transfusions, so major bleeding events are primarily defined using only inpatient diagnostic codes for bleeding. Still, an exploratory outcome on bleeding requiring transfusions will be assessed in the US databases, where transfusion procedures are expected to be more reliably captured. Furthermore, common bleeding definitions used in randomized trials require laboratory parameters to categorize bleeding events, but as this information is not consistently available from EHD sources, bleeding scales were not used in in ALETHEIA. Since comprehensive information on mortality is available in US Medicare claims but not in Optum Clinformatics and IBM MarketScan, additional meta‐analyses of outcomes, whether or not these outcomes include death, will be performed as a sensitivity analysis in a restricted study population, excluding patients from the Optum and MarketScan databases. The rationale is to provide results for both the bleeding and CV outcomes in populations with similar age distributions.

Fourth, the 5000 person‐years on treatment threshold is considered as the minimum number required for sufficient precision in clinical outcome assessment. While this threshold is expected to be met, person‐years on treatment is a function of both time on treatment and number of patients, and is thereby influenced by the databases' available duration of longitudinal data as well as their national coverage.

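### The sensitivity meta-analysis prompted by incomplete mortality data still includes the Italian database, which has no dates for out-of-hospital deaths

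*Protocol article*

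**What the plan says.** Section 2.5 sets the outcome: "The secondary CV composite outcome is defined as the composite of hospitalization for MI or stroke", together with death from any cause. The same section adds three-point MACE, and defines fatal bleeding, CHD death and CV death as a death within 28 days of a relevant admission. All of these need a date of death.

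Table 3 in Section 2.3 describes how each source captures deaths:

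- **Optum:** "comprehensive data on mortality is not available in the Optum Clinformatics database".
- **MarketScan:** "comprehensive data on mortality is not available in the MarketScan database".
- **ReS (Italy):** in-hospital deaths are dated, but "For deaths in the outpatient setting, neither date of death nor cause of death is recorded in ReS".
- **Medicare:** "Data on mortality are available".
- **UK, Sweden and Germany:** each is described with a source of death information and no stated gap.

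On pooling, Section 2.7 says of the meta-analyses: "analyses will be applied to combine estimates derived from each country/database". Fixed effects is the main method, and random effects is also run.

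The third limitation in the Discussion contrasts Medicare with Optum and MarketScan on mortality. It then announces additional sensitivity meta-analyses "excluding patients from the Optum and MarketScan databases". These cover outcomes with and without a death component, and the stated rationale is comparable age distributions for the bleeding and CV results. Italy's gap is mentioned neither there nor elsewhere in the limitations.

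**The concern.** The plan recognises that pooling death outcomes over databases that miss deaths is a problem, and it sets up an analysis in response. It applies that reasoning to two of the three sources that its own Table 3 flags. The third, ReS, ties with no other source and ranks third by projected size, after Medicare and MarketScan.

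A death at home in Italy is lost from the numerator. In the on-treatment analysis it looks like a discontinuation, dated under Section 2.4 at the last prescription plus its supply plus 7 days. In the intention-to-treat analysis it does not end follow-up, so the patient goes on accruing event-free time. The 28-day definitions are affected to the extent that patients die outside hospital after discharge.

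At stake is how the restricted result will be read. A reader will take it as the version in which death capture has been dealt with. It would still carry part of the error, and differences between databases would mix true risk with completeness of death recording.

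**Working it through.** **Inputs (Table 3, projected patients).** Optum 750, MarketScan 1,200, Medicare 3,100, UK 250, Sweden 800, Germany 150, Italy 1,000.

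**The plan's own total.** 750 + 1,200 + 3,100 + 250 + 800 + 150 + 1,000 = 7,250, which matches the stated figure.

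**Shares in sources with incomplete deaths.**

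- Restricted pool as planned: 7,250 − 750 − 1,200 = 5,300. Italy's share is 1,000 / 5,300 = 18.9%.
- All seven sources: (750 + 1,200 + 1,000) / 7,250 = 2,950 / 7,250 = 40.7%.
- Restricted pool without Italy: 3,100 + 250 + 800 + 150 = 4,300.

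**Illustrative bias in all-cause mortality, restricted pool.** The documents give no capture fraction. Assume that a fraction c of Italian deaths is captured, that capture is complete in the other four sources, that true rates are equal and that person-time is proportional to patients. Then

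relative bias = (4,300 + 1,000 × c) / 5,300 − 1.

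- c = 0.6: 4,900 / 5,300 − 1 = −7.5%.
- c = 0.4: 4,700 / 5,300 − 1 = −11.3%.

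**Dependence on the pooling scale.** The plan pools database estimates and does not pool crude person-time. At c = 0.5:

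| Weighting | Calculation | Bias |
|---|---|---|
| Person-time | 4,800 / 5,300 − 1 | −9.4% |
| Inverse variance, raw rate | 5,300 / (4,300 + 1,000 / 0.5) − 1 | −15.9% |
| Inverse variance, log rate | exp[500 × ln(0.5) / 4,800] − 1 | −7.0% |

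The sign is the same in all three; the size is not.

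**Composite, restricted pool.** Assuming deaths make up 30–50% of composite events and 30–70% of Italian deaths are missed, the three weightings give a rate about 2–9% too low.

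**Precision after dropping Italy.** Take the 2.5 per 100 person-years that Section 2.8 expects for MACE, and assume 1 year per patient. The 95% interval is 2.5 ± 1.96 × √events / (N / 100).

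- N = 5,300: 132.5 events, half-width 1.96 × 11.51 / 53 = 0.43, interval 2.07–2.93.
- N = 4,300: 107.5 events, half-width 1.96 × 10.37 / 43 = 0.47, interval 2.03–2.97.

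**Composition after dropping Italy.** Medicare is 3,100 / 4,300 = 72% of the pool, against 3,100 / 5,300 = 58% as planned.

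**The case against.** Several points on the other side have force.

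- **The restricted analysis is not purely a mortality repair.** Its stated rationale is age comparability, and it also covers bleeding. That is correct. It is nonetheless introduced by the lack of mortality data in two sources, and Italy's gap is of the same kind.
- **The effect is modest.** On the composite, 2–9% is smaller than the random error, since a half-width of 0.43 is 17% of 2.5. This is fair and bears on severity. But the interval does not reflect the bias, and more person-years would not reduce it.
- **The plan is partly transparent already.** Table 3 discloses the ReS gap, forest plots show each database, heterogeneity is explored before pooling, and cause-of-death outcomes have death-certificate sensitivity analyses in the UK and Sweden. These let a careful reader see Italy's estimate. They do not take the missing deaths out of the pooled figure.

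A reader might also infer something stronger: that the headline pooled composite and mortality rates certainly include all three deficient sources and are understated by a known, large percentage. The documents do not support that. Section 2.7 refers to every country or database in general terms and does not list databases by outcome. Section 2.3 says mortality data are used where available. The age rationale could also mean that the main death outcomes already leave out Optum and MarketScan, with the extra analysis putting bleeding on the same population. Inclusion is the likelier reading, because the exclusion appears only in an additional sensitivity analysis, but it remains an inference. On either reading, nothing in the article takes Italy out.

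**Conclusion.** The point holds for the restricted meta-analysis. Table 3 states that ReS lacks dates for out-of-hospital deaths, and the restricted pool keeps ReS at 1,000 of 5,300 projected patients (19%). Rates for outcomes with a death component are therefore biased low there. The downward direction is certain for the Italian estimate. For the pooled figure it follows under the equal-rates assumption used above.

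The size is an illustration only. All-cause mortality is about 8–11% low if 40–60% of Italian deaths are captured and estimates are weighted by person-time, and other weighting scales shift that figure. For the main pool, 2,950 of 7,250 patients (41%) is an upper limit on the share in affected sources, because the article does not name the databases behind each death outcome.

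This is a should-fix matter. The composite is a secondary outcome, the study is descriptive and makes no outcome comparison between cohorts, and bleeding requiring hospitalization has no death component.

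**What to change.** For the CV composite, all-cause mortality, three-point MACE, fatal bleeding, CHD death and CV death:

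1. Exclude ReS as well as Optum and MarketScan from the restricted meta-analysis, leaving Medicare, UK, Sweden and Germany (4,300 projected patients).
2. Present the Optum, MarketScan and ReS estimates for these outcomes separately, labelled as lower bounds.
3. State which databases enter the main pooled analysis of each death outcome.
4. Add Italy's gap to the limitations, next to the one already given for the two US sources.

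The cost is a change of wording and one further pooling run. Intervals widen slightly, from about 2.07–2.93 to 2.03–2.97 per 100 person-years on the assumptions above. The remaining pool is 72% Medicare and so probably older. If bleeding is still reported over a wider set of databases, the age comparability that the plan wants is weakened. Running bleeding on the same four sources as a companion result would keep it.

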## Data Availability

Data sharing not applicable as no data were generated or analysed during the current study.
